### Recruitment of group therapists and group facilitators

It is planned to recruit geropsychologically qualified psychotherapists as study therapists via training institutions for psychotherapy with older adults. For the control group, certified senior citizen assistants (i.e., lower-qualified professionals supporting and caring for older adults in the community such as in senior citizens’ centres, parishes or at home) will be recruited.

### Recruitment of participants

A variety of strategies will be used to inform the target population about the study: In addition to leveraging the existing pool of prospective patients within the university’s psychotherapy outpatient clinics in Berlin and Siegen, a multifaceted approach involving self-referral and gatekeeper-referral strategies is planned. Specifically, it is intended to promote the study throughout Germany via articles in newspapers. We aim to inform health professionals as gatekeepers, including staff from geriatric and geropsychiatric hospitals and day clinics, general practitioners, as well as psychotherapists.

Prospective study participants can access information about the study VISION-AGE via the project website (www.vision-age.de). The study website provides key inclusion criteria to help interested individuals conduct an initial self-assessment of their eligibility and they can take a depression self-test using the Depression im Alter Skala (DIA-S) [41], without transmitting their data to the study centre. Individuals expressing interest in participating in the study are invited to contact the research team via telephone or a contact form on the study website. In the first step, their name and email address are collected exclusively for the purpose of study-related communication, such as the dissemination of study information and the first scheduling-appointment. The contact details are therefore entered into the study data capture system, which initiates the dispatch of an email containing instructions for study registration (including the provision of informed consent to participate in the study) on our primary data collection platform. The email also contains links to the study information and to available mental health crisis support services (each provided via a separate link, viewable without registration). Upon successful registration, participants receive an appointment for an enrolment interview, during which the study is presented and eligibility is assessed. In the absence of a response within a reasonable timeframe, the data is deleted.

### Inclusion criteria and accompanying measurement

The research team conducts enrolment interviews via videoconference with interested individuals to assess their suitability for the study. Therefore, at T0, measurement instruments that do not represent outcome variables are used to prevent selection bias based on the outcome measures themselves. Participants will be included in the study if they have the capacity to give informed consent, voluntarily agree to participate, and meet the following criteria: [a] they are aged 68+ (with no upper age limit); [b] they are diagnosed with mild or moderate unipolar depressive symptoms associated with one of the following ICD-10 diagnoses: F32.0/1, F33.0/1, F38.1/8, F41.2 or F43.2 based on a clinical interview; [c] they have clinically relevant depressive symptoms based on self-report; [d] they are not taking psychoactive medications or are taking a stable dosage for at least six weeks prior to study entry; [e] they have an indication for participation in group psychotherapy; [f] sufficient language and communication skills in German and [g] a functioning, stable internet connection and basic IT skills.

Participants diagnosed with severe depression are excluded from the study, as their condition necessitates more intensive care to ensure patient safety. Furthermore, the online format demands a substantial degree of autonomy, a quality that probably be hindered by severe depression. In addition, group-based interventions must take into account the potential burden on other participants that may arise from the intense self-disclosures of severely depressed participants.

Participants will be excluded from the study if: [a] they have very severe depressive symptoms based on the clinical interview (F32.2 or F33.2) or self-report; [b] they have very severe anxiety symptoms or symptoms of panic disorder or specific phobia that mandate in vivo exposure; [c] they report acute suicidal tendencies; [d] they show signs of, or have been diagnosed with dementia or mild cognitive impairment; [e] they report psychotic or bipolar symptoms or have been diagnosed with bipolar disorder or schizophrenia; [f] they have a physical illness in the terminal phase; or [g] they plan to change their intake of psychoactive medications before enrolment or during the study. Further reasons for exclusion include [h] receiving psychotherapy while participating in the study, [i] communication difficulties and visual or hearing impairments that would severely affect an individual’s ability to participate in the study. The reasons for excluding participants will be recorded.

During enrolment interviews, participants are asked to provide personal (contact) details such as age, address and phone number. In addition, information on pre-existing mental and physical comorbidities, current medication as well as relevant socio-demographic variables, is requested. Self-report measures of depressive and anxiety symptoms are collected via the Hospital Anxiety and Depression Scale (HADS) [42]. A HADS score of ≥ 8 is considered clinically relevant for the depression subscale, while a score of > 18 on either the depression or anxiety subscale indicates a very severe manifestation of that subscale. Depressive symptoms of clinical severity (i.e. a score of ≥ 4 on a 0–8 scale) and associated diagnoses are assessed using the section depression from the Diagnostisches Interview bei psychischen Störungen (Structured Clinical Interview for Mental Disorders, DIPS) [43], slightly adapted for the purpose of present study. Cognitive function is assessed using a slightly adapted version of the Mini Mental Status Test (MMST) [44], a screening tool for cognitive impairment. A score of MMST < 25 is considered to be (mild) cognitive impairment. An indication for participation in group therapy is assessed in the clinical impression, based on the assessment of whether the individual person with their symptoms, themes and personality could benefit from group exchange. Participants are assumed to have a stable internet connection and basic IT skills if they can register independently, provide digital informed consent and attend the enrolment interview.

Finally, the severity of the depressive disorder (mild or moderate) and the presence or absence of anxiety symptoms are assessed based on clinical judgement after all enrolment diagnostics have been carried out.

### Randomization and blinding

Participant eligibility is determined during the enrolment interview by a member of the research team, based on the inclusion and exclusion criteria. This information will be communicated to the participant and recorded in the data capture system. Following this evaluation, suitable participants are then randomly assigned to a study condition using a computer-generated simple randomisation algorithm. The research team has no influence on the allocation of suitable participants to one of the conditions. Within the specified conditions, patients are manually allocated to a block of four participants each, taking into account their time availability for group therapy. After the enrolment interview digital visits via videoconference will be carried out at baseline (T1) and post-treatment (T6) and FU (T7) by members of the research team who will be blinded to the group allocation and previous test results. The study data capture system implements a role-based access concept to ensure that details of group allocation and participants’ recorded data are only accessible to the Principal Investigator (PI) and research team members responsible for supervision.

### Intervention

Participants will find out in the first group session whether they have been assigned to the IG or the CG. Both programmes include 20 weekly online group appointments (with each session lasting 100 min, including a 10-min break) in a fixed group of four, as well as four additional individual meetings with group therapist (in the IG) or group facilitator (in the CG). Participants must join the meetings using their own devices, such as personal computers or tablets. If more than two participants permanently withdraw from a therapy group (e.g., due to illness or lack of motivation), the remaining participants will be offered the opportunity to switch to another group.

To prevent bias and buffer against potential investigator allegiance effects, group therapists and group facilitators are not part of the research team and do not conduct measurements with the participants. They are trained in a two-day pre-intervention workshop to ensure adherence to the respective manual and are regularly supervised by the research team based on session videos. In order to verify the integrity of the treatment, a sample of 10% of all sessions is evaluated by raters who are unaware of the study hypotheses, condition, and session number. Thereby adherence to the study protocol is evaluated using a 20-item adherence scale derived from the two manuals (10 Items IG, 10 Items CG). In addition, the session-documentation is regularly checked for manual-consistency.

### Intervention-group VISION-AGE

VISION-AGE is a standardised, age-sensitive group psychotherapy programme carried out via video conference by trained psychotherapists. The treatment manual was tested in the psychotherapeutic university outpatient clinic of the MSB Medical School Berlin during a three-year pilot phase and was refined in an iterative process based on clinical experiences and patient feedback. There was no evidence of any negative therapy effects. The manual focuses on promoting self- and developmental regulation strategies and thereby addresses the three biographical ‘time corridors’ past - present - future. Well-established LRT methods are enriched by CBT and PP techniques. In addition to the 20 group sessions, four individual sessions (each 45 min long) are intended to reinforce the therapeutic alliance and deepen the content of the group sessions. The initial upstream module focuses on reflecting upon and modifying existing images and experiences of ageing, as well as addressing ageism, in order to build the motivation necessary for change (Module 1 Positive self-perceptions of ageing), followed by Module 2 Life-review, Module 3 Life-management and Module 4 Life-planning. An accompanying handbook is sent to participants prior to the intervention, providing preparatory tasks related to specific sessions of the manual (e.g. collecting photos for the LRT sessions or a gratitude exercise for the Life-management sessions). For an overview of the therapeutic manual’s contents and the postulated mechanisms of action, see the supplemental material.

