**Further exploratory measures**								
• Working Alliance (WAI-SR)					x			
• Group Cohesion (FEPiG)					x			
• Programme Satisfaction (ZUF-8)							x	x
• Pre-programme: Assessment of individual therapeutic goals (across five categories); Post-programme: Goal attainment scale		x					x	x
• Assessment of medical resource utilization (self-developed questionnaire)		x					x	x
• Health-related life quality (EQ-5D-5L)		x					x	x
• Acceptance of video technology (TUQ)			x	x	x	x	x	x
• Assessment of health-related changes (self-developed questionnaire)		x	x	x	x	x	x	x
**Safety relevant data**	Notification is possible at anytime.							

Note. **T0** = Enrolment, afterward Allocation, **T1** = Baseline assessment, **T2–T5** = intermediate assessment, **T6** = post-treatment assessment, **T7** = FU assessment

The data collection will be conducted on seven time points to assess the short- and medium-term effects of the VISION-AGE-intervention, and will be identical for both the IG and CG. The assessment points include:

A baseline assessment prior to the start of the intervention;Following completion of the first module (Positive self-perceptions of ageing, i.e., group session 4);Following the second module (Life-review, i.e., group session 10);Following the third module (Life-management, i.e., group session 15);Following the fourth module (Life-planning, i.e., group session 19);Two weeks after the end of the programme (i.e., group session 20); and Six months post-programme (FU).

To encourage continued participation, the study participants receive greeting cards, which include memories of the group sessions, once they have completed all six assessment points.

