### Primary outcomes

The primary outcome variable is the reduction in participants’ depressive symptoms, as indicated by changes in their self-reported scores on the Patient Health Questionnaire-9 (PHQ-9) [45] between pre- and post-treatment (T1–T6) and FU (T1–T7). The PHQ-9 is recorded at each measurement point T1–T7.

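### The therapy handbook sent before the programme can reveal the arm before the first group session, and nothing stops it arriving before the post-allocation baseline PHQ-9

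*Protocol article*

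**What the plan says.** All references are to the protocol article.

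- **Allocation.** Randomization and blinding places it directly after the eligibility decision at the enrolment interview: "Following this evaluation, suitable participants are then randomly assigned to a study condition using a computer-generated simple randomisation algorithm". Table 3 marks allocation in the T0 column, and its note defines T0 as "Enrolment, afterward Allocation".
- **Baseline.** The baseline visit (T1) comes after the enrolment interview. Primary outcomes states: "The PHQ-9 is recorded at each measurement point T1–T7". There is no PHQ-9 at T0. Under Assessment, T1 is placed only before the programme begins. The mediators (Table 3) and the individual therapy goals (Further exploratory measures) also start at T1.
- **Disclosure of the arm.** Intervention states: "Participants will find out in the first group session whether they have been assigned to the IG or the CG".
- **Handbook.** The section on the VISION-AGE arm states: "An accompanying handbook is sent to participants prior to the intervention, providing preparatory tasks related to specific sessions of the manual". Its examples are "collecting photos for the LRT sessions or a gratitude exercise for the Life-management sessions". The Control group section does not mention a handbook.
- **Use of T1.** The primary outcome is the change in self-reported PHQ-9 from T1 to T6 and from T1 to T7. The contrast of interest in the analysis section is the IG's pre-post change set against the control group's (CG's).

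**The concern.** A baseline taken after allocation is still a fair reference point as long as participants do not know their arm when they complete it. The plan relies on this, because it delays disclosure to the first group session. A handbook built around therapy tasks, received before that session, can undo the delay.

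If it arrives before T1, two things could move the IG's T1 scores: knowing that one has been given psychotherapy, and starting the tasks early. The PHQ-9 is self-reported, so blinding the T1 assessor does not protect it. The tasks also belong to modules whose target strategies are measured as mediators from T1, so the mediation hypothesis has the same exposure. Randomisation balances what happens before allocation. It cannot balance a shift that arises in one arm afterwards.

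**Working it through.** The point concerns the order of events, so the sections are set side by side first. The arithmetic then shows only how a shift would carry through.

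**1. Order of events**

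| Event | Timing fixed by the article |
|---|---|
| Eligibility, T0 measures including HADS | Enrolment interview (T0) |
| Allocation | After the eligibility decision, T0 column of Table 3 |
| T1: first PHQ-9, mediators, goals | After T0, before the programme |
| IG handbook | Before the programme |
| Participant told the arm | First group session |

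Two sequences fit this text:

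- (a) allocation, T1, handbook, session 1
- (b) allocation, handbook, T1, session 1

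In both, an IG participant can know the arm before session 1, which contradicts the Intervention section. Only in (b) is T1 exposed. Nothing in the article rules (b) out, and nothing says it will happen.

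**2. How a T1 shift enters the contrast**

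Write the contrast as a difference in reductions:

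D = (T1_IG − T6_IG) − (T1_CG − T6_CG)

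Hold the T6 scores and the CG's T1 fixed. If T1_IG moves by δ, D moves by δ. A lower (improved) IG baseline makes δ negative and biases against the IG. A higher (worse) one makes δ positive and biases in its favour.

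**3. The plan's own figures**

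- Sample size: 200 / (1 − 0.20) = 250, as planned.
- Power for d = 0.45 with 100 per arm, two-sided 5%: Φ(0.45/√(2/100) − 1.96) = Φ(3.18 − 1.96) = 0.889. This agrees with the stated power above 0.80 for the main contrast.

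**4. Illustration**

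The size of δ is an assumption; the article gives none. It is expressed in the same SD unit as d = 0.45, which is a further assumption because the article does not say which SD standardises d.

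- Power if the IG baseline improves: Φ((0.45 − |δ|)/√(2/100) − 1.96).
- Two-sided rejection rate with no true effect: Φ(|δ|/√(2/100) − 1.96) + Φ(−|δ|/√(2/100) − 1.96).

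| Assumed shift, SD | D if IG baseline improves | Power | D if IG baseline worsens | Rejection rate with no true effect |
|---|---|---|---|---|
| 0 | 0.45 | 0.889 | 0.45 | 0.050 |
| 0.05 | 0.40 | 0.807 | 0.50 | 0.064 |
| 0.10 | 0.35 | 0.697 | 0.55 | 0.109 |
| 0.15 | 0.30 | 0.564 | 0.60 | 0.186 |
| 0.20 | 0.25 | 0.424 | 0.65 | 0.293 |

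A shift of 0.10 SD is 0.10/0.45 = 22% of the planned difference. In the last column, the excess rejections favour the IG only if its baseline worsened. If it improved, they favour the CG.

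**The case against.** The strongest reply is that the article never says the handbook arrives before T1. Sending it after T1 and shortly before session 1 fits every sentence, and a dispatch date is the kind of detail that an article leaves to the full protocol. This stands against any claim that the baseline is compromised. It does not remove the conflict over when the arm becomes known, because both of those statements are in the article.

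Further points that stand:

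- **Control-arm material.** A reader might infer that the CG receives nothing. The article is only silent on this. A CG dispatch with its own content could equally reveal the arm, so only arm-neutral material would preserve disclosure at session 1.
- **Direction.** A reader might infer a risk of a falsely positive trial. The most natural mechanism, early benefit from the tasks, would lower the IG's T1 score and bias against the IG. The sign is not known.
- **Allocation before baseline.** This is not an error in itself. The plan pairs it with delayed disclosure, blinded assessors and restricted access to allocation. Randomization and blinding and Table 3 agree with each other.
- **Loss between allocation and T1.** A reader might infer that such participants have no baseline information. They lack a PHQ-9, but HADS and a clinical severity rating are taken at T0, before allocation, and could inform the planned imputation.
- **Disclosure to the rater.** Participants know their arm at T6 and T7 in any case, so the handbook adds this risk only at T1.

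**Conclusion.** Two things are firm. Allocation precedes the first PHQ-9, and the article gives two incompatible accounts of when an IG participant can learn the arm. It follows that nothing in the article protects T1 from a handbook that arrives first.

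The stronger reading, that masking is broken before baseline, is not supported, because T1 and the dispatch of the handbook are not ordered. The supported statement is that masking can be broken.

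The resulting bias in the difference in pre-post change equals the shift in the IG's T1 score. Its size and sign are unknown. The range of 0.05 to 0.20 SD is illustrative only, and it assumes that T6 scores and the CG baseline stay unchanged. If T1 is always completed before dispatch, the baseline bias disappears. The contradiction about disclosure then remains, as does the possibility that people who know their arm leave before session 1 at different rates.

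The point still merits a change, because T1 is the reference for the primary and secondary outcomes and the protection is nearly free.

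**What to change.** 1. State that the handbook is released only after T1 is complete and locked and the arm has been disclosed, at or after the first group session. Alternatively, send arm-neutral material to both arms before then.
2. Reconcile the Intervention section with the section on the VISION-AGE arm so that both give the same moment of disclosure.

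The cost is one release rule. Preparation time should suffer little: by the article's own schedule the life-review module follows group session 4 and the life-management module follows session 10, so both quoted tasks belong to later sessions.

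Completing T1 before randomisation is an alternative that protects the baseline whenever the handbook is sent. It has a real cost. Groups of four are formed by hand within arm after allocation, according to availability, so the gap between baseline and session 1 could lengthen. It would also leave the disclosure conflict to be settled separately. Table 3 needs changing only if this alternative is chosen.

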### Control group

The active CG is a non-clinical group discussion programme designed to provide social support and stimulation through group discussions in a supportive, non-judgemental environment. During the first half of each session, participants discuss personal, everyday issues from the previous week, followed by a discussion of stimulating, neutral topics such as hobbies, cooking, or animal companionship. Group facilitators encourage engagement and socialisation among group members, similar to the type of support participants might receive in a community support group at a senior citizens’ centre. The manual is based on one used in a previous study [36], where it showed a small positive effect on depression and anxiety in older patients, and has been adapted and expanded for the present study. The CG programme will be delivered by senior assistants, as the work requirements align with their usual work tasks and no clinical skills are necessary. To achieve the same therapeutic dosage as the IG, the time allocated to group therapy sessions is identical to that of the IG. In terms of individual contact, participants will receive four five-minute friendly digital meetings with their group moderator, as well as four additional 40-minute audio features offering stimulating content related to the preceding sessions (e.g., about the benefits of having an animal companion). See the supplemental material for an overview of the group discussion manual, including the discussion topics.

### Data acquisition, data management and data archiving

Participant data will be collected using a Primary Data Collection Tool based on MEDITyme^®^ platform technology as a web-based application, supplied by XPERTyme GmbH (Wessling, Germany). The platform has been developed to incorporate all the necessary features to enable secure video communications and to support the compliant collection, transmission, and storage of study data. It is designed to ensure compliance with Good Clinical Practice (GCP) and General Data Protection Regulation (GDPR) requirements. All source data and informed consent forms will be directly documented and stored on the platform, following predefined standardised processes. Since no additional source data are generated at the study sites, on-site monitoring is not required. In order to minimise errors in data entry and ensure data quality, the system incorporates predefined data entry rules and validation checks. Access to the platform is restricted to authorised study personnel and participants according to predefined roles and responsibilities and blinding specifications. For example, group therapists and group facilitators are only permitted to see the data of their own group participants. Any subsequent corrections are digitally documented and fully traceable through an audit trail. The group sessions and qualitative interviews will be recorded and subsequently stored in order to facilitate the supervision and qualitative analysis of the data.

The process evaluation will be conducted through continuous monitoring of data integrity, adherence to the informed consent procedure, and verification of protocol compliance by the Principal Investigator (PI), who has full access to all study data of all participants. Protocol deviations identified during monitoring will be documented and addressed according to CAPA (Corrective and Preventive Action) procedures.

In the primary data system, all members of the research team can view, within each participant’s history, whether the participant attended a group session (without any specific role assignment, only the session number, no content), a digital visit, or completed a questionnaire (attendance only, without access to the content). Thus, information on participant adherence is available without unblinding the research team. Due to the program’s regular group sessions, the group therapists and facilitators have a clear overview of participants’ adherence, which is discussed routinely during supervision meetings. The Primary Data Collection Tool enables automated reminder emails to be sent to participants, and in cases of dropout, telephone contact may be initiated to inquire about continued interest in participation.

Once the intervention phase is completed, following the last participant’s assessment, the technical support team by XPERTyme GmbH will generate two datasets from the study`s data capture before closing it: one with the source data and one with the relevant pseudonymized study data, suitable for statistical analysis. Both datasets will be protected with a checksum and archived separately from each other at the Medical School Berlin (MSB). Both the source data and the raw dataset will be retained for a minimum of 10 years in accordance with regulatory requirements. In addition, a member of the research team will generate a de-identified dataset from the pseudonymized data. After the retention period has expired, all records containing personal information will be securely deleted or destroyed, except for the de-identified dataset, as they no longer contain any personal reference. Access to identifiable information is strictly limited and may only be granted to auditors, or ethics committees for oversight purposes.

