### Termination criterion

If a participant withdraws their informed consent during the study, as termination criteria, all data collected up to that point will be removed from the analysis dataset, with the deletion duly documented.In addition, participation in the study may be terminated early under the following circumstances:If a participant does not wish to continue participating or cannot be reached, or fails to attend required study visits (drop-out);If a participant starts an ambulant psychotherapy between the assessment points T0 and T7;If a participant changes their psychoactive medication, continued study participation will be reviewed on a case-by-case basis in consultation with the participant and PI;If health problems arise that are not related to the study content, but may hinder focus-targeted or regular study participation, continued study participation will be reviewed on a case-by-case basis in consultation with the participant and PI. This includes new or worsening physical complaints (e.g. a fall followed by hospitalization), serious events (e.g. the unexpected death of a family member) or psychological complaints (e.g. acute grief – except for depression and anxiety, which are dealt with under point [f]);If any SAE occur, decisions regarding continued participation will always be made by the PI in consultation with the IDSMB, to ensure the participant’s well-being and the appropriateness of their involvement. The jointly made decision will be transparently communicated to the participant;If a participant passes away during the study period;If the PI or study sponsor decides to discontinue participation for specific reasons.

In the event of early termination, the termination criteria are recorded on an individual basis, specifying the corresponding time point and category.

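### The PI sees allocation and accumulating outcome scores and also has a role in ending participation, so removals and supervision can be influenced by arm and emerging results

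*Protocol article*

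**What the plan says.** **Access.** Under Randomization and blinding, the article states that "details of group allocation and participants’ recorded data are only accessible to the Principal Investigator (PI) and research team members responsible for supervision". Under Data acquisition, data management and data archiving, the PI carries out continuous monitoring and is described as the person "who has full access to all study data of all participants". Under Primary outcomes, the PHQ-9 is recorded at every point from T1 to T7, so primary-outcome scores build up during treatment.

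**Who is shielded.** The T1, T6 and T7 visits are done by "members of the research team who will be blinded to the group allocation and previous test results". Under Intervention, therapists and facilitators are kept out of the research team and take no measurements, with the stated purpose: "To prevent bias and buffer against potential investigator allegiance effects". The PI is not described as blinded.

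**Ending participation (Termination criterion).**
- Medication change: "If a participant changes their psychoactive medication, continued study participation will be reviewed on a case-by-case basis in consultation with the participant and PI".
- Health problems unrelated to the study content: the same case-by-case review with participant and PI.
- Serious adverse events (SAEs): the PI decides in consultation with the IDSMB, and the decision is described as joint.
- Open clause: "If the PI or study sponsor decides to discontinue participation for specific reasons". No criterion and no independent step is attached.

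The category and time point of each termination are recorded.

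**The concern.** The article recognises investigator allegiance as a risk and protects two groups against it, the assessors and the group leaders. The PI, who takes part in decisions on who stays in the study, has no comparable protection and can see both arm and scores. One SAE category under Safety considerations is acute worsening of depressive symptoms, so one trigger for a removal decision lies in the domain of the primary outcome.

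Two things are at stake. First, if similar events are judged differently by arm or by how a participant is doing, T6 and T7 values could be selectively missing. The article speaks of ending participation in the study and does not say whether outcome assessment continues afterwards. Second, the research team supervises the group leaders of both arms, and supervising members may see recorded data as well as allocation. Knowledge of an emerging difference could influence supervision, and no choice of analysis set corrects that.

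**Working it through.** **The plan's own figures (Power and sample size).** With 200 analysable participants and 20% dropout, 200 / (1 - 0.20) = 250, as stated. For 100 per arm and d = 0.45 at two-sided 5% (sidedness assumed), the noncentrality is 0.45 x sqrt(100/2) = 3.18. Power is then Phi(3.18 - 1.96) = 0.889, consistent with the stated power above 0.80. The present point does not question these figures; d = 0.45 serves only as the yardstick.

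**Illustration of the bias.** The documents give no number of discretionary removals, so all inputs except d are assumptions: no true effect, 100 per arm, outcome SD of 1, a fraction f of one arm removed and not assessed further, and those removed being the worst of that arm.

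*Step 1: no imputation.* Removing the worst fraction f shifts that arm's mean by phi(z) / (1 - f), with z the upper f quantile of the standard normal.
- f = 2%: 0.049 SD, two-sided rejection under no effect about 6%
- f = 5%: 0.103 / 0.95 = 0.109 SD, about 12%
- f = 10%: 0.195 SD, about 27%

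This is not the planned primary analysis. Statistical analysis sub-study 1 specifies ITT with multiple imputation compatible with the analysis model.

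*Step 2: imputation from a recorded interim score.* Simulation with 4,000 runs per setting and an interim-final correlation of 0.7 (assumed). The final score is regressed on the interim score among those retained in the affected arm. That arm's mean is then re-estimated at the interim mean of everyone randomised to it. This is a simple stand-in for the planned imputation, and its rejection rates are approximate.

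| Removed from one arm | Removal depends on recorded interim score: bias (rejection) | Removal tracks the unrecorded final outcome: bias (rejection) | Second bias / 0.45 |
|---|---|---|---|
| 2% | 0.001 SD (5%) | 0.033 SD (6%) | 7% |
| 5% | 0.002 SD (5%) | 0.056 SD (6%) | 13% |
| 10% | 0.002 SD (5%) | 0.112 SD (13%) | 25% |

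The ratios use the unrounded biases: 0.0325 / 0.45 = 0.07, 0.0564 / 0.45 = 0.13, 0.1121 / 0.45 = 0.25.

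**Reading.** Selection that the recorded scores explain is essentially removed. Selection by judgement not captured in the data is only partly removed. At 5% the bias falls from 0.103 SD without imputation (same simulation) to 0.056 SD.

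**The case against.** The strongest reply is that arm and PHQ-9 scores are recorded data. If the PI acts on them, the resulting missingness can be explained by what was observed, and the planned imputation deals with it. The simulation confirms this, provided the interim PHQ-9 values enter the imputation model. A reader might take the step 1 shifts as the bias of the primary result; the documents do not support that, because the primary analysis is ITT with multiple imputation. All illustrated figures also put every removal in one arm and in one direction, which is close to a worst case.

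Other stronger readings also fail:
- That the PI alone decides on removals for safety. SAE decisions involve the IDSMB, and the medication and health reviews involve the participant and are not labelled as safety decisions. Only the open clause lacks any second party, since either the PI or the sponsor can invoke it.
- That the PI selects the per-protocol set. Planned statistical analyses defines that set by attendance, so early removal can affect it only indirectly.
- That the IDSMB already holds the unblinded outcome data. Safety considerations gives it progress, safety, data integrity and protocol adherence, and does not mention unblinded outcomes.

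There are real safeguards: blinded assessors, recorded termination categories, an audit trail, and role-based access with blinding specifications. What remains is judgement that leaves no trace in the scores, influence on supervision, and an open clause without a stated ground.

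**Conclusion.** The point stands as a design weakness worth correcting. The article itself fixes both the PI's access and the PI's role in ending participation, so this is not a detail left to another document. Removals and supervision can be influenced by arm and emerging results; nothing in the document shows that they will be.

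For the primary analysis, the part explained by recorded scores is largely repaired. The illustrative residual from unrecorded judgement is about 0.03, 0.06 and 0.11 SD for 2%, 5% and 10% of one arm, against a planned 0.45. This rests on the assumed correlation of 0.7, one-sided removal of the worst outcomes, and no assessment after removal. The true number of removals is unknown. The influence on supervision cannot be quantified from the documents.

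**What to change.** 1. Until database lock, set the platform's existing roles so that the PI and supervising team members do not see PHQ-9, MADRS, GAS or SPWB values by arm. Individual safety information stays available to those who need it. Completeness can be checked on completion status, which the data-management section already shows without content. Any unblinded outcome summaries go to the IDSMB only, and this should be written into its remit.
2. Continue T6 and T7 assessment after participation in the programme ends, unless consent is withdrawn, and report discretionary removals by arm and category. This is needed alongside item 1: the PI would still know allocation, and supervisors would still see session videos, so hiding scores does not by itself prevent unrecorded judgement.
3. Reconcile the open clause under Termination criterion with the grounds listed there and with the aim of buffering allegiance effects stated under Intervention. The clinical grounds themselves are for the trial team to set.

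Cost: a change of role settings, some added wording, and some extra follow-up of participants who leave the programme. The PI loses routine sight of outcome scores during the trial.
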